##### Physical activity promotion

2.3.1.2

Participants will complete three weekly home training sessions that will not coincide with supervised training days. Each session will last 20 min, they will complete two sets of five exercises, with one minute of work and one minute of rest.- Day 1
1.Sitting and standing up from a chair.2.Lateral lunge.3.Supine bicycle.4.Elbow flexion with weights.5.Lateral shoulder raises.- Day 2
1. Lunge.2. Quadriceps wall isometric.3. Glute bridge.4. Frontal shoulder raises.5. Wall push-ups.- Day 3
1.Walking on tiptoes.2.2. Squats.3.Knee-to-chest raises.4.Abdominal crunch.5.Shoulder press with weights.

Additionally, all participants should walk for 60 min each day of the week.

#### Control group

2.3.2

The control group will only perform the physical activity promotion program 5 days/week. This will be combined with walking for 60 min every day of the week.

### Outcomes

2.4

During the initial assessment, all variables, including sociodemographic factors, will be measured. After the intervention period, all outcome variables will then be evaluated again.

Personal and sociodemographic variables are as follows:
•Age (years)•Gender (male/female)•Weight (kilograms), height (meters) and body mass index (kg/m^2^)•Time since diagnosis (years and months)•Diagnosis (CLL or small lymphocytic lymphoma)•IGHV mutational status (mutated/unmutated)•Number of prior lines of treatment•Current treatment and dose•Time under current treatment (months)•Chromosome 17p deletion and *TP53* mutation status prior to current treatment (present/absent)•Current treatment under clinical trial (yes/no)

#### Primary outcomes

2.4.1

The primary outcome measure will be frailty: Frailty will be assessed using the Short Physical Performance Battery (SPPB) scale (27), which includes three components: a balance test, gait speed, and a chair stand test. The scale has a maximum score of 12 points, with higher scores reflecting better physical function.

#### Secondary outcomes

2.4.2

The secondary outcomes are as follows:
•Quality of life: Quality of life will be evaluated using the European Organization for Research and Treatment of Cancer Quality of Life Questionnaire (EORTC QLQ). The EORTC QLQ-C30 is a widely used tool designed to assess quality of life in patients with cancer (28). Comprising 30 items, this questionnaire divides 24 items across five functional domains: physical, role, emotional, cognitive, and social. Additionally, it includes three symptom-related scales—fatigue, pain, and nausea/vomiting—and a global health status scale. Six further items evaluate other symptoms, including dyspnea, appetite loss, insomnia, constipation, and diarrhea, as well as financial burden. Patients respond to items using a four-point scale (“not at all”, “a little”, “quite a bit”, “very much”), except for the overall health and quality-of-life scales, which use a seven-point format. On the functioning and overall health and quality-of-life scales, higher scores reflect better health status. In contrast, higher scores on the symptom scales indicate a greater level of symptom burden. In addition, a specific questionnaire was used to measure quality of life in patients with CLL, the EORTC QLQ-CLL17 questionnaire. The EORTC QLQ-CLL17 includes 17 items, which are organized into three multi-item subscales: symptom burden from disease and/or treatment (six items), physical condition and fatigue (four items), and health-related worries or fears about functioning (seven items, with two being conditional). The conditional items pertain to work or education and are only rated by patients if relevant to their situation. Each item is rated on a four-point scale (“not at all”, “a little”, “quite a bit”, and “very much”), reflecting experiences over the past week (29). The scoring method for the QLQ-CLL17 follows that of the EORTC QLQ-C30, with items in each subscale summed and converted to a standardized scale from 0 to 100. Higher scores across all scales and individual items indicate greater levels of symptoms or issues.•Anxiety and depression: Anxiety and depression will be evaluated using the Hospital Anxiety and Depression Scale HADS, a well-established and validated questionnaire (30) for various populations. HADS includes a total of 14 items, with seven questions dedicated to assessing anxiety (subscale A) and the other seven focused on depression (subscale D), each rated on a scale of 0–3. This structure provides separate scores for anxiety and depression.•Fatigue: Fatigue will be evaluated using the 13-item Functional Assessment of Cancer Therapy-Fatigue (FACT-F) subscale (31), a self-reported tool designed to measure the severity of fatigue in cancer patients (32, 33). This widely used scale for assessing cancer-related fatigue combines 27 items from the FACT-General section with 13 additional items specific to fatigue, resulting in a score range from 0 to 160. Higher scores on the FACT-F indicate less fatigue.•Sleep quality: Patient sleep quality will be assessed using the Athens Insomnia Scale (AIS), a self-administered tool consisting of eight items developed by Soldatos (34) and validated for use in the Spanish population (35). The first five items assess “sleep disturbances”—specifically, sleep onset, nocturnal awakenings, early morning awakening, total sleep duration, and overall sleep quality—corresponding to criterion “A” for insomnia diagnosis under the ICD-10 classification of mental and behavioral disorders. The last three items evaluate “daytime consequences”, such as daytime well-being, physical and mental functioning, and daytime sleepiness, aligned with criterion “C” of the ICD-10. Each item is rated on a Likert scale from 0 (“no problem”) to 3 (“significant problem”), yielding a total score range of 0–24. Higher scores reflect more severe impairment, with a score of ≥6 indicating the presence of insomnia (36).•Physical activity: The overall physical activity will be measured with the Spanish version of the International Physical Activity Questionnaire (IPAQ) (37). The IPAQ includes seven questions designed to assess the duration and frequency of physical activities at different intensity levels: Light activity (<600 MET minutes/week), such as walking at home, at work, or leisure walking; Moderate activity (600–3,000 MET minutes/week), which includes activities like cycling, playing tennis, or carrying light loads; Vigorous activity (>3,000 MET minutes/week), involving high-intensity exercises such as aerobic workouts, digging, or heavy lifting. Additionally, the IPAQ evaluates inactivity over the past week, providing a comprehensive view of the participant's physical activity levels. The total PA score is the sum of vigorous, moderate, and light PA in MET minutes/week (38).•Body composition: The collection of various variables related to the body composition of the participants will be carried out. Height will be measured using a measuring rod. The other variables will be obtained using the electrical bioimpedance technique, using the TANITA BC-418® device. Variables to be collected include total body weight and appendicular muscle mass (ASM), which is defined as the sum of the muscle mass of each limb. To calculate the appendicular muscle mass index (ASMI), the height-adjusted appendicular muscle mass formula (AMM/height^2^) will be applied (8). In addition, parameters such as visceral fat, body fat percentage (BF%) and body mass index (BMI) will be assessed. To ensure the accuracy of the data, all participants will be weighed with the minimum amount of clothing and barefoot, which minimizes variations in the measurements and ensures that the results are representative of their actual body composition (39).•Strength: The strength of both the lower and upper limbs will be assessed. The Jamar® dynamometer (J00105 Lafayette Instrument Company, USA), a hydraulic dynamometer considered the gold standard in the evaluation of grip strength, will be used (40). Both hands will be measured. The measurement will be performed following the Southampton Protocol (41). The patient will be seated in a chair with a backrest and the test will be explained to them. Three consecutive measurements will be taken on the same hand with a duration of 5 s per contraction and with an interval of 10 s between measurements. Encouraging commands will be given during the test to squeeze harder. The patient shall be seated in a chair with backrest, shoulder adducted and neutrally rotated, elbow flexed at 90°, forearm in neutral position and wrist in slight extension (0°–30°). The second Jamar® position shall be selected for all participants, with the exception of small hands which shall be placed in the first position and reported. The Jamar® measurement shall always be performed by the same evaluator. The mean/maximum value of each hand will be selected for analysis. The assessment of lower extremity strength will be conducted through the Five-Repetition Sit-to-Stand Test (5STS), a functional test that quantifies the capacity to rise and sit from a chair without the use of the arms, thereby reflecting lower extremity strength. An armless folding chair with a seat height of 17 in (43.2 cm) will be utilized. The time taken to complete the five repetitions will be recorded from the moment the subject rises from the chair to the moment they return to the sitting position (42).•Physical performance: In addition to the SPPB, walking speed is assessed as a measure of physical performance associated with frailty using the four-meter walk test (4MWT). The patient starts walking one meter before the start line, where the stopwatch is activated, and is instructed to maintain his or her usual speed until four meters past the finish line. The test is performed three times, and the best value is recorded (43).

### Sample size

2.5

The sample size was determined based on functional capacity, assessed by the Short Physical Performance Battery (SPPB) with scores ranging from 0 to 12 points (27). According to previous research in subjects with similar characteristics, 1.34 points has been established as a substantial minimum demonstrable change, in order to avoid detection of small and irrelevant changes (44). Furthermore, in studies with interventions shorter than 12 weeks, with similar participants, the standard deviation of the SPPB has been estimated to range between 1 and 1.5 points (45, 46).

Considering these data, the sample size calculation to detect a difference equal to or greater than 1.34 points on the SPPB, with a standard deviation of 1.3 points, accepting an alpha risk of 0.05 and with a power of 80%, requires 18 participants in each group, also assuming a loss rate of 15%. This calculation was performed with GRANMO software version 7.12.

### Allocation and randomization

2.6

The randomization process for this clinical trial will be conducted using Microsoft Excel 2020, which generated a list of random numbers for participant assignment. Each participant will be allocated a unique number from this list: participants with odd numbers were assigned to the experimental group, and those with even numbers to the control group. This method ensures a randomized and balanced distribution between groups, reducing potential bias and enhancing the validity of the trial results. This process will be carried out by a member of staff from the Haematology Department of the Hospital Universitario de Salamanca who is not involved in the research.

### Blinding

2.7

Given the study design, blinding of participants and evaluators to the intervention will not be feasible. However, to maintain objectivity, statistical analysis will be performed by an independent statistician who is unaware of the participants' group assignments.

### Statistical methods

2.8

For the descriptive analysis, data normality will be assessed using the Kolmogorov–Smirnov and Shapiro–Wilk tests (applicable for samples where *n* < 30). Variables following a normal distribution will be characterized by mean, standard deviation, and range, while non-normally distributed variables will be represented by median and interquartile range. Qualitative variables will be described through frequencies and percentages.

In terms of quantitative analysis, Pearson's correlation coefficient will be used to confirm the validity of the assessment procedures chosen for this study, and Cronbach's alpha will verify their reliability. For comparisons between two means, we will employ Student's *t*-test (a parametric test for independent samples), the Mann–Whitney *U*-test (a non-parametric test for two independent samples), and Wilcoxon's test (a non-parametric test for paired data). For comparisons across three or more means, an ANOVA will be used for independent groups (parametric with Snedecor's *F*-test and non-parametric with the Kruskal–Wallis *H*-test). For repeated measures, Snedecor's *F*-test will be applied to parametric data, while Friedman's test will be used for non-parametric data. Correlations will be analyzed using Pearson's correlation for normally distributed data and Spearman's correlation for non-normally distributed data.

To identify variables associated with outcomes of interest, a multivariate logistic regression analysis will be conducted. This model will include variables that are either significant in the bivariate analysis or pertinent to the study. For qualitative or categorical variables, contingency tables and the Chi-square test will be used for comparisons involving two independent samples.

*p*-value of less than 0.05 will be considered statistically significant, indicating a confidence interval of 95%. Analyses will be performed using IBM SPSS Statistics, version 28.0.1.

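### Section 2.8 asks Pearson's correlation to establish validity and Cronbach's alpha to establish reliability, which neither statistic can do for the measures listed (minor; primary comparison unaffected)

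*Protocol article*

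**What the plan says.** Section 2.8 of the protocol article gives both the statistics and the conclusions they are to yield: "Pearson's correlation coefficient will be used to confirm the validity of the assessment procedures chosen for this study, and Cronbach's alpha will verify their reliability". The second statement refers back to the assessment procedures as a whole and is not limited to questionnaires. The section gives no reference measure, expected size of r or acceptance level for either statistic. Its only general decision rule is in the closing paragraph, where a p-"value of less than 0.05 will be considered statistically significant".

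Section 2.4 shows what would be covered. The primary outcome is the SPPB, "which includes three components: a balance test, gait speed, and a chair stand test". Among the secondary outcomes, "The assessment of lower extremity strength will be conducted through the Five-Repetition Sit-to-Stand Test (5STS"), recorded as the time for five repetitions. Walking speed is measured separately by the four-metre walk test (4MWT): "The test is performed three times, and the best value is recorded". Grip strength is measured three times per hand. Body composition comes from a bioimpedance device, with no repeat readings described. The other instruments include multi-item questionnaires (QLQ-C30, QLQ-CLL17, HADS, FACT-F, Athens Insomnia Scale).

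**The concern.** The test of a Pearson correlation has a true correlation of zero as its null hypothesis. Rejecting it shows that two measures are not unrelated. It does not show that they measure the same construct, that they agree, or that either measures what it is meant to measure. Alpha describes how consistently a set of items hangs together, so it says nothing about a measure that consists of one number.

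The overlap in the outcome list adds to the problem. Gait speed and chair rising are parts of the SPPB and are also measured as separate outcomes. A correlation between the SPPB total and either of them is partly a correlation of a quantity with itself.

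At stake is a possible statement in the trial report that the measures, including the primary one, were shown to be valid and reliable in CLL. Data from about 36 patients, analysed this way, could not support it.

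**Working it through.** **Inputs from the article.** Total n = 36 (18 per group). Loss rate 15%, so 36 × 0.85 = 30.6, or about 30 completers. Significance level 0.05, taken as two-sided because the article does not say. **Not in the article:** the true correlations and the pairs to be correlated. Both are assumptions below, shown over a range.

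**1. The plan's own sample size.** n per group = 2 × [1.3 × (1.960 + 0.842) / 1.34]² = 14.8, rounded up to 15. Allowing for loss, 15 / 0.85 = 17.6, rounded up to 18. The stated 18 per group reproduces. (A t-based calculation gives 15.8, then 15.8 / 0.85 = 18.6, so 19 at most.) The validity check plays no part in this calculation.

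**2. The correlation that reaches p < 0.05.** |r| = t / √(n − 2 + t²), with t the 97.5% point on n − 2 degrees of freedom.
- n = 36: t = 2.032, so |r| = 2.032 / √(34 + 4.130) = 0.329 and r² = 0.11. The Fisher-z 95% interval at that r runs from about 0.00 to 0.59.
- n = 30: t = 2.048, so |r| = 2.048 / √(28 + 4.196) = 0.361 and r² = 0.13. The interval runs from about 0.00 to 0.64.

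**3. How often p < 0.05 would occur** (bivariate normal data, 200,000 simulated samples per value, close to the Fisher-z approximation):

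| True correlation | n = 36 | n = 30 |
|---|---|---|
| 0.1 | 9% | 8% |
| 0.2 | 22% | 19% |
| 0.3 | 44% | 37% |
| 0.4 | 69% | 61% |
| 0.5 | 89% | 83% |
| 0.7 | >99% | >99% |

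These figures are power, not error rates, because the null is false in every row. The chance passes one half at a true correlation of about 0.33 (n = 36) or 0.36 (n = 30).

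**4. Built-in correlation, if SPPB were paired with one of its own components.** For three uncorrelated components of equal variance, the correlation of one with the sum is 1/√3 = 0.58. This reaches p < 0.05 in about 97% of samples at n = 36 and about 94% at n = 30. A less favourable case assumes components scored coarsely 0 to 4 (cut points −2, −1.5, −0.8 and 0 on a standard normal trait) and a separately timed test correlating 0.9 with that trait. The mean r is then about 0.45, and the figures are 82% and 74%. All of this arises with components that share nothing.

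**5. What a demanding criterion would need.** For the lower 95% limit of r to exceed 0.5, the observed r must be at least tanh(0.549 + 1.96/√(n − 3)), which is 0.71 at n = 36 and 0.73 at n = 30.

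**6. Where alpha applies.**
- Multi-item questionnaires: items exist and alpha is suitable.
- One 5STS time or one bioimpedance reading: no items, so alpha cannot be computed.
- Grip and 4MWT: the analysed value is a single number per hand or per test (mean or maximum for grip, best for the walk). The three underlying trials allow a reliability estimate if all are kept.

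**The case against.** The strongest reply is that the article nowhere makes p < 0.05 the test of validity. It names the coefficient, and the 0.05 sentence is a general convention that is not attached to this check. The size of r may be what is judged, and comparators and thresholds may sit in a full protocol or analysis plan that is not shown. This stands. A reader might infer that significance is the sole criterion, but the text does not say so, and the percentages above hold only if that rule is applied.

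A reader might also infer that weakly related measures would usually be declared valid. The figures do not support it. At true correlations of 0.1 to 0.3, significance occurs in only 8% to 44% of trials, so such measures would usually fail.

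Nor does the article say that SPPB will be correlated with 5STS or 4MWT. The part-whole figures are conditional on that choice.

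Alpha is a standard choice for most of the questionnaires. It can be computed for the SPPB from its three components, and across repeat trials of grip or walking if those are retained. Instrument validation is not an objective of the trial, and section 2.4 already cites sources for its instruments, describing HADS and the Athens scale as validated.

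What the reply does not remove is the mismatch in the stated text. A fuller plan could add pairs and thresholds. It could not make a correlation establish validity, or give alpha items to work on in a single reading.

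**Conclusion.** The point holds as a mismatch between the statistics named and the conclusions promised, not as an omission. Correlations in 30 to 36 patients can describe association. They cannot confirm validity, and under the general 0.05 rule an |r| of 0.33 to 0.36 would pass. Alpha does not fit the single-value measures. The size rests on a two-sided test, roughly normal data and one pooled correlation. The part-whole range of 74% to 97% also needs SPPB to be paired with an overlapping test, under the assumptions shown.

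A reader might go further and conclude that the trial's main result is undermined. It is not: the check does not enter the between-group SPPB comparison or the sample size, which reproduces. The consequence is confined to what may be claimed about the instruments. Minor priority.

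**What to change.** Replace the sentence in section 2.8 as follows.
- Remove the claims to establish validity and reliability, and rely on the published sources already cited for the instruments.
- Report baseline correlations between measures descriptively, with 95% confidence intervals and no verdict from a p-value. Do not present the SPPB total against 5STS or 4MWT as validity evidence.
- Restrict Cronbach's alpha to the multi-item questionnaires.
- For grip strength and 4MWT, report the intraclass correlation coefficient and the standard error of measurement from the three baseline trials already taken.

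The cost is a few lines of wording and some extra output, with no new patients or assessments. The trial gives up a claim of in-sample validation, and all three repeat trials must be entered in the database rather than only the selected value.

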### Intervention

2.3

The exercise intervention program has been tailored for participants diagnosed with CLL undergoing active treatment. To ensure appropriate methodological quality and replicability of the exercise program, the Consensus on Exercise Reporting Template (CERT) (25) guidelines will be followed for a detailed description of the intervention (Supplementary Table S2). It primarily emphasizes resistance training, while also incorporating daily aerobic activities. This intervention will span a duration of 8 weeks. The study sample will be randomly split into two groups: the intervention group and the control group, as described below.

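### No primary SPPB comparison is singled out, and none of the listed between-group tests adjusts for the baseline SPPB that the trial measures

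*Protocol article*

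**What the plan says.** The primary outcome is SPPB (section 2.4.1): "Frailty will be assessed using the Short Physical Performance Battery (SPPB) scale". It is a bounded score: "The scale has a maximum score of 12 points, with higher scores reflecting better physical function".

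It is measured twice. Section 2.4 says of baseline: "During the initial assessment, all variables, including sociodemographic factors, will be measured". It says of follow-up: "After the intervention period, all outcome variables will then be evaluated again". Section 2.3 fixes the interval: "This intervention will span a duration of 8 weeks".

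Section 2.5 sizes the trial on a mean difference: "the sample size calculation to detect a difference equal to or greater than 1.34 points on the SPPB". It uses an SD of 1.3, alpha 0.05, 80% power and 15% loss, and arrives at 18 per group. It does not say whether 1.3 is the SD of the score or of the change.

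Section 2.8 lists tests for all outcomes together. For two means: "For comparisons between two means, we will employ Student's *t*-test (a parametric test for independent samples"; then the Mann-Whitney U-test; "and Wilcoxon's test (a non-parametric test for paired data". Repeated measures get an F-test or Friedman's test, depending on whether the data are treated as parametric. The only multivariable model is a logistic regression to find variables associated with outcomes. Section 2.8 does not mention SPPB.

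**The concern.** Two arms measured before and after treatment can be compared on the follow-up score, on the change, or on the follow-up score adjusted for baseline. These have different precision, and in a single trial they can give different answers. Section 2.8 admits the first, may admit the second through the repeated-measures test, and does not include the third.

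Two things are at stake.

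- **Precision.** With about 15 completers per arm, baseline SPPB is probably the most informative covariate available. A follow-up comparison that leaves it out keeps the chance baseline difference as noise in the estimate.
- **A fixed analysis.** If the follow-up and change analyses are both open once the data are seen, the nominal 5% error no longer holds. The candidates also differ in what they estimate. Mann-Whitney does not estimate the mean difference of 1.34 on which the trial is sized, and the paired Wilcoxon test does not compare the arms.

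**Working it through.** **Inputs from the protocol.** Difference 1.34, SD 1.3, alpha 0.05 (taken as two-sided), power 80%, loss 15%, 18 per group (section 2.5); one baseline and one post-intervention assessment (section 2.4).

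**Assumption.** The correlation r between baseline and follow-up SPPB is not given. I use 0.3, 0.5 and 0.7. Because the meaning of the SD is open, both readings are shown.

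**Step 1: the plan's own figure.** n = 2 × (1.960 + 0.842)² × 1.3² / 1.34² = 14.77, so 15 per group. With 15% loss, 15 / 0.85 = 17.6, so 18. The stated number reproduces as an unadjusted two-sample comparison. A one-sided test would need 12, or 15 after loss, which does not match.

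**Step 2: power with 15 completers per arm.** Noncentral t, with noncentrality 1.34 / (SD × √(2/15)); 28 degrees of freedom, or 27 for ANCOVA.

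*Reading A: 1.3 is the SD of the score.* Follow-up SD = 1.3; change SD = 1.3√(2(1−r)); ANCOVA residual SD = 1.3√(1−r²).

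| r | Follow-up t-test | Change score | ANCOVA |
|---|---|---|---|
| 0.3 | 78% | 63% | 81% |
| 0.5 | 78% | 78% | 88% |
| 0.7 | 78% | 94% | 97% |

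*Reading B: 1.3 is the SD of change.* Follow-up SD = 1.3/√(2(1−r)); change SD = 1.3; ANCOVA residual SD = 1.3√((1+r)/2).

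| r | Follow-up t-test | Change score | ANCOVA |
|---|---|---|---|
| 0.3 | 90% | 78% | 92% |
| 0.5 | 78% | 78% | 88% |
| 0.7 | 56% | 78% | 84% |

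ANCOVA has the highest power in every row. (The 78% rather than 80% arises because the sample-size formula uses the normal approximation.)

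**Step 3: chance imbalance (reading A).** The SE of the baseline difference is 1.3 × √(2/15) = 0.47, so its 95% range is ±1.96 × 0.47 = ±0.93 points. An unadjusted follow-up comparison carries r times that: ±0.47 at r = 0.5 (35% of 1.34) and ±0.65 at r = 0.7 (49%).

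**Step 4: type I error when the choice is open.** In simulations with 15 per arm (6,000 trials per scenario; r = 0.5 and 0.7; normal scores, and scores rounded and capped to 0-12):

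- Choosing between the t-test and Mann-Whitney by Shapiro-Wilk gave a type I error of 4.8% to 5.4%.
- Taking the better of the t-test and Mann-Whitney gave 5.6% to 6.1%.
- Taking the best of follow-up t-test, Mann-Whitney and change-score t-test gave about 10%. A separate simulation of rounded scores gave 8.7% to 9.2%.

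**The case against.** **The unadjusted test is valid.** Under randomisation it is unbiased, and the stated 18 per group is right for it. This stands: the sample size is not wrong, and ANCOVA adds precision rather than correcting an error. The imbalance in step 3 is likewise already inside the t-test's standard error. It is imprecision, not bias.

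**The gain depends on an unknown correlation.** This also stands. At r = 0.3 under reading A the gain over the follow-up t-test is under 4 points.

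**The plan does not ignore baseline altogether.** The repeated-measures F-test could be read as a mixed ANOVA. With two arms and two time points, its group-by-time test equals a change-score comparison. Under reading A at r = 0.7 that leaves only 94% against 97%. But no group-by-time term is stated, and change scores do worse than the plain follow-up test when r is below 0.5.

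**Naming the primary test may be left to a fuller document.** Partly so. However, section 2.8 does commit to particular tests, and the between-group ones it names are unadjusted.

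Three stronger readings are tempting but not supported:

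- *Normality tests decide between the t-test and Mann-Whitney.* That is likely, but the text places those tests under the descriptive analysis and states no such rule for two means. Such a gate would also keep type I error near 5% (step 4).
- *The result may be off by 0.93 points, 69% of the target.* That is the range of the baseline imbalance, not the part carried into the follow-up comparison.
- *Efficacy will be claimed from within-arm tests.* A paired test is listed, but nothing says a treatment claim will rest on it.

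**Conclusion.** The point holds as a should-fix improvement, not as an error that invalidates the trial. Section 2.8 does not fix which listed test is the primary SPPB comparison, and its between-group tests leave out a baseline covariate that the trial already collects.

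For correlations of 0.3 to 0.7, ANCOVA gains about 4 to 19 points of power over the follow-up t-test if 1.3 is the SD of the score. If 1.3 is the SD of change, it gains about 6 to 14 points over the change-score test. These figures assume 15 completers per arm, a true difference of 1.34, equal SDs at both visits and approximately normal scores. The ranking is firmer than the size of the gain: ANCOVA comes out ahead of both alternatives at every correlation examined from 0.3 to 0.8, under either reading of the SD.

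The error-rate concern is confined to an open choice between follow-up and change analyses, where it reaches about 9-10%.

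**What to change.** State in section 2.8 one primary analysis: ANCOVA of 8-week SPPB on randomised group and baseline SPPB, reported as an adjusted mean difference with 95% CI. Because SPPB is a bounded integer score, add a rank-based or permutation version as a prespecified sensitivity analysis. Use the same model for continuous secondary outcomes. Label paired within-arm tests as descriptive.

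The cost is one degree of freedom and a change of wording. It needs no new data, visits or participants, and 18 per group can stay. The change should be made before outcome data are seen.

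### The secondary search for associated variables uses a logistic model with significance-based entry, although nearly all outcomes are numeric scores and about 30 completers are expected

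*Protocol article*

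**What the plan says.** Section 2.8 (Statistical methods) sets the purpose and the model in one sentence: "To identify variables associated with outcomes of interest, a multivariate logistic regression analysis will be conducted". The entry rule follows: "This model will include variables that are either significant in the bivariate analysis or pertinent to the study". The general threshold in that section is a p-"value of less than 0.05 will be considered statistically significant". No other regression model is named, no limit is put on the number of terms, and the analysis is not called exploratory.

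The outcomes are defined in section 2.4. For the primary outcome, SPPB, the text reads: "The scale has a maximum score of 12 points, with higher scores reflecting better physical function". It gives no threshold for a binary version. The secondary outcomes are also numeric: EORTC scales, HADS, FACT-F, AIS, MET-minutes, body composition, grip strength, chair-stand time and walking speed. Two of them come with categories. The AIS is given "with a score of ≥6 indicating the presence of insomnia", and the IPAQ has three activity bands, divided at 600 and 3,000 MET minutes per week.

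Section 2.5 plans 18 patients per group with 15% loss.

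**The concern.** There are two problems, and they compound each other.

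The first is the form of the model. Binary logistic regression needs a two-class outcome. For SPPB and almost every secondary outcome, someone must cut the score in two before the model can be fitted. This throws away information that a linear model would keep, and it makes the result depend on where the cut is placed.

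The second is the entry rule. A variable admitted because it reached p < 0.05 in these data is then estimated and tested in the same data. Its coefficient is on average too far from zero, because only large chance deviations pass the screen. Its interval is too narrow, because the final model treats the selected terms as if they had been fixed in advance. Both effects are worst in small samples.

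At stake is the credibility of any statement about which patient characteristics go with a good or poor outcome. Section 1 says the trial should help establish evidence-based clinical intervention protocols, so such statements may well be read as guidance.

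**Working it through.** **Inputs from the protocol article.** Difference 1.34, SD 1.3, alpha 0.05, power 80%, loss 15%, 18 per group (section 2.5); 36 in total (Abstract); 11 bullets of personal and sociodemographic variables (section 2.4); significance threshold 0.05 (section 2.8).

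**Assumptions not in the document.** A two-sided test; 5 to 10 events per term as a rule of thumb; 11 to 20 independent noise candidates for the illustration.

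**1. The plan's own sample size.** n per arm = 2 × (1.96 + 0.84)² × 1.3² / 1.34² = 14.8, rounded up to 15. With 15% loss, 15 / 0.85 = 17.6, rounded up to 18. The stated figure is reproduced.

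**2. Completers.** 36 × 0.85 = 30.6, so about 30.

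**3. Terms the data can carry.** The limiting number is the size of the smaller outcome class.

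| Patients in smaller class | Terms at 10 events per term | Terms at 5 events per term |
|---|---|---|
| 15 (even split, the best case) | 1.5 | 3 |
| 10 | 1 | 2 |

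The randomised group uses one of these terms if it is included.

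**4. Chance of a false entry.** With k independent candidates unrelated to the outcome, the chance that at least one passes the screen is 1 − 0.95^k.
- k = 11: 1 − 0.95^11 = 0.43, with 11 × 0.05 = 0.55 false entries expected.
- k = 20: 1 − 0.95^20 = 0.64, with 1.0 expected.

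**5. What the final model then shows.** This was simulated with 30 patients, 10 to 15 in the smaller class, pure-noise candidates, a bivariate screen at 0.05, and then logistic regression on the variables that passed.
- 11 candidates: the final model contains a nominally significant predictor in about 30% of trials. Where something was selected, the apparent AUC is about 0.76, although the true value is 0.50.
- 20 candidates: about 40–45% of trials, with an apparent AUC of about 0.78–0.79.

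**6. The other route of entry.** Variables may also come in as pertinent. This avoids the screen but does not limit the model. Forcing in 11 noise variables gives an apparent AUC of about 0.85, and about 10% of fits separate or fail to converge.

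**7. Cost of dichotomising.** Splitting a normally distributed score at its median keeps 2/π = 64% of the information. This is only a guide, since SPPB is a bounded integer score and no median split is stated.

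**The case against.** The strongest reply is that this is a side analysis, described briefly in a condensed article. Its stated purpose is to find associated variables. Means are compared between groups with Student's t or the Mann–Whitney test, and section 2.5 rests on a mean difference. Section 2.8 also provides Pearson and Spearman correlations, which use the scores undivided. The outcomes meant for the logistic model are not named, and a fuller document could define binary versions; the 1.34-point change in section 2.5 might serve as a responder threshold, although it is not declared as one. Subject-matter entry is allowed alongside significance. The 11 bullets hold more than 11 variables, and these are correlated (BMI is computed from weight and height), so 43% is not a property of this trial.

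Much of this stands, and it limits the point in three ways.
- A reader might infer that the odds ratios will be reported as the adjusted treatment effect. The text does not say so.
- A reader might infer that the trial loses power for its primary comparison. Under normality, dichotomising SPPB would lower power from about 81% to 53–58%, but only if a binary analysis replaced the two-group test of the score, which the plan does not propose.
- A reader might infer that AIS is the only outcome with categories. The IPAQ bands are given too, although three bands do not make a ready binary outcome.

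The reply does not remove the core. Cut-offs and a covariate list may fairly be left to another document, but the logistic form and the significance-based entry rule are choices that this text makes. The correlations are univariable and do not repair the multivariable model.

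**Conclusion.** The point holds for the secondary association analysis and no further. The prescribed model does not suit outcomes that are almost all numeric, and the prescribed entry rule is unreliable with about 30 completers. At best about 15 patients fall in the smaller class, enough for roughly one to three terms, while the rule sets no upper limit.

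The completer count follows from the plan's own figures. The number of terms rests on a rule of thumb. The false-entry chances of 43% (11 candidates) to 64% (20 candidates) assume independent noise variables and show the order of the problem; they do not predict this trial's result. The direction of the bias, with coefficients too far from zero and intervals too narrow, does not depend on those assumptions. The two-group comparison of SPPB and the sample size of 18 per group are unaffected.

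**What to change.** Amend the regression paragraph of section 2.8 as follows.

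1. For numeric outcomes, replace the logistic model with linear regression on the score after the intervention, with randomised group, the baseline value of that score and at most one or two covariates named before the data are seen.
2. Delete the rule that admits variables because they were significant in bivariate analysis.
3. Keep logistic regression only for an outcome defined as binary in advance, for example AIS of 6 or more, with few terms.
4. Label the search for associated variables as exploratory.

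The cost is analysis wording only: no extra patients, visits or measurements. The price is that fewer candidate predictors are examined in the multivariable model, which is small, since about 30 patients cannot support many. Other candidates can still be described with the correlations already planned.
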